#### 8.4 ADVERSE EFFECTS

Although no adverse effects are expected, recording the number (and percentage) of events and their severity will be contemplated for each trial arm.

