### 5.3 DIETARY INTERVENTION

The intervention group participants will receive information, motivation, and support to modify their dietary habits according to the Atlantic Diet. To ensure good adherence, a recipe book based on local products has been developed, with detailed recipes created by a chef and evaluated by a team of nutritionists. The nutritionists will provide recommendations to help the intervention subjects adjust their daily and weekly food intakes to meet both the Atlantic Diet and general consensus recommendations. Participants will be encouraged to use the provided recommendations and recipes during the study period, and a day-long cooking course with a chef will also be offered. Additionally, a telephone helpline will be available to address any questions or concerns.

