## 5.7 STATISTICAL INTERIM ANALYSES AND TRIAL HALTING

Since in this study no adverse effects were expected, and given that it lasted 6 months, no guidelines for interruption were planned nor were any interim analyses performed.

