## 5.8 TIMING OF OUTCOME ASSESSMENTS

The intervention period will last 6 months. The schedule of study procedures is given in [Table 1](#). [Table 2](#) summarizes the information that will be collected, as well as the tests that will be performed, over the study period.

[Table 1](#). Graphical representation of the intervention

| Time line       | Intervention                                                                                                                                                                                                                                                                       | Control                                                                                                                                                                                       |
|-----------------|------------------------------------------------------------------------------------------------------------------------------------------------------------------------------------------------------------------------------------------------------------------------------------|-----------------------------------------------------------------------------------------------------------------------------------------------------------------------------------------------|
| Pre- assessment | [figure not shown]                                                                                                                                                                                                | [figure not shown]                                                                                                          |
| Basal (time 0)  | [figure not shown]
Randomization
[figure not shown]
[figure not shown] | [figure not shown]
Randomization
[figure not shown] |
| 1 week          | [figure not shown]                                                                                                                                                                                                |                                                                                                                                                                                               |

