| [figure not shown] | Distribute book with educational material and recipes                                                                                                                                                                                                                                |
| [figure not shown] | Nutrition education course (30-40 min) provided to individual families by nutritionists; recommendations for adults and children; information on eating five meals per day; preparing menus; explain the Atlantic diet and food pyramid; benefits of physical activity; how to limit |

|                                                                                     |                                                                                                                                                                                                                                                          |
|-------------------------------------------------------------------------------------|----------------------------------------------------------------------------------------------------------------------------------------------------------------------------------------------------------------------------------------------------------|
|                                                                                     | sedentary activity; how to use the education material provided                                                                                                                                                                                           |
| [figure not shown]   | Diary with food delivery dates (every 3 weeks)                                                                                                                                                                                                           |
| [figure not shown]   | Begin delivery of food packages (adapted for the number of family members)                                                                                                                                                                               |
| [figure not shown]   | Complete questionnaire on food habits, consumption of delivered foods, physical activity/sedentarism, answering any questions                                                                                                                            |

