| [figure not shown]   | Group session (2 h) by researchers and nutritionists to explain influence of lifestyle on health, changing to a healthier diet, importance of physical activity, characteristics of the traditional Atlantic diet, patterns for designing a healthy diet |
| [figure not shown]   | Cooking class led by teaching chefs; recommendations on portion size                                                                                                                                                                                     |
| [figure not shown] | Gift of food basket, educational material and recipe book                                                                                                                                                                                                |

188  
189

190 **Table 2.** Outcomes and measurement time points.

|                                                    | Baseline | 3 months | 6 months |
|----------------------------------------------------|----------|----------|----------|
| Questionnaires & Health Measurements    |          |          |          |
| Sociodemographic data                              | ✓        |          |          |
| Health status: personal and family medical history | ✓        |          |          |
| Quality of life, (SF-12v2 questionnaire)           | ✓        |          | ✓        |
| Dietary habits, FFQ                                | ✓        |          | ✓        |
| 3-day food record                                  | ✓        |          | ✓        |
| Diet quality                                       | ✓        |          | ✓        |
| Dietary patterns                                   | ✓        |          | ✓        |
| IPAQ-short                                         | ✓        |          | ✓        |
| Sedentary behavior                                 | ✓        |          | ✓        |
| Drinking habits (AUDIT-C questionnaire)            | ✓        |          | ✓        |
| Use of tobacco                                     | ✓        |          | ✓        |
| Anthropometry                               |          |          |          |
| Body weight (kg)                                   | ✓        | ✓        | ✓        |
| Height (cm)                                        | ✓        | ✓        | ✓        |

|                                  |   |   |   |
|----------------------------------|---|---|---|

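### Per-arm adverse-event counts are contemplated with no scheduled question to collect them, and only intervention families have extra contacts, so unsolicited reports would be open to unequal ascertainment

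*Protocol*

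**What the plan says.** Protocol section 8.4 consists of one sentence: "Although no adverse effects are expected, recording the number (and percentage) of events and their severity will be contemplated for each trial arm". It gives no definition of an event, no question, no time point and no between-arm test.

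Section 5.7 relies in part on the same expectation: "Since in this study no adverse effects were expected, and given that it lasted 6 months, no guidelines for interruption were planned".

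Section 5.8 sets out the schedule. "The intervention period will last 6 months", and both arms have Table 1 entries at baseline, 3 months and 6 months. The rows for weeks 1, 4, 7, 10, 13, 16, 19 and 22 have an entry in the intervention column and an empty control cell. The legend includes food deliveries every 3 weeks and this item: "Complete questionnaire on food habits, consumption of delivered foods, physical activity/sedentarism, answering any questions". Table 2, titled "Outcomes and measurement time points", lists questionnaires, anthropometry and laboratory tests.

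Section 5.3, on the dietary intervention, adds that "a telephone helpline will be available to address any questions or concerns". Section 5.1 says that control families take part in none of the intervention activities and receive no food.

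**The concern.** A number and percentage of events per arm can be interpreted only if events were looked for, and looked for alike in both arms. The protocol schedules no such enquiry. Events would then reach the file mainly when a participant happens to mention them, and intervention families have far more occasions to do so.

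Two readings of the resulting figures would be unsafe. A higher percentage in the intervention arm could reflect more contact and not more harm. A low percentage in either arm could not support a statement of safety, because no scheduled question would have elicited the events.

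The matter is not trivial for a dietary trial of this kind. The donated foods listed in section 5.1 include red and white wine, and section 7.2 admits family members from age 3 to 85. An expectation of no adverse effects should be open to checking against data. This is a matter of data collection: a statistical analysis plan cannot recover events that were never elicited.

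**Working it through.** The protocol states no adverse-event rate, so there is no figure of its own to reproduce. The check is a comparison of sections, followed by an illustration on assumed values.

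**1. Is there a scheduled enquiry?**
- Table 1 legend: consent, blood sampling, anthropometry, blood pressure, questionnaires (quality of life, activity, diet, alcohol, tobacco), food records, education, deliveries and classes. There is no adverse-event item.
- Table 2: no adverse-event row. Personal and family medical history is ticked at baseline only, so no listed item updates it at 3 or 6 months.

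**2. Are opportunities to report equal?**

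| | Intervention | Control | Source |
|---|---|---|---|
| 3- and 6-month entries | 2 | 2 | Table 1 |
| Further weekly rows with an entry | 8 | 0 | Table 1 |
| Food deliveries every 3 weeks | yes | no | Table 1 legend; 5.1 |
| Helpline | yes | none described | 5.3 |

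Post-baseline contacts are thus up to 8 + 2 = 10 against 2. Ten is an upper count. The symbols in the Table 1 cells cannot be read, a delivery need not be an interview, and week 13 falls at about the time of the 3-month visit.

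**3. What could that do to the counts?** Assume equal true risk in both arms and a probability c that an event is captured at any one contact. The captured share after k contacts is 1 − (1 − c)^k, with k = 2 for control and k = 10 for intervention. The documents give no value for c, so a range is shown.

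| c (assumed) | Control, 1 − (1 − c)² | Intervention, 1 − (1 − c)¹⁰ | Apparent ratio |
|---|---|---|---|
| 0.05 | 9.8% | 40.1% | 4.1 |
| 0.1 | 19.0% | 65.1% | 3.4 |
| 0.2 | 36.0% | 89.3% | 2.5 |
| 0.3 | 51.0% | 97.2% | 1.9 |
| 0.5 | 75.0% | 99.9% | 1.3 |
| 0.9 | 99.0% | 100.0% | 1.01 |

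Example: with a true risk of 10% in both arms and c = 0.1, the expected observed percentages are 10% × 0.190 = 1.9% and 10% × 0.651 = 6.5%.

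If week 13 and the 3-month visit are one contact, k = 9. At c = 0.1 the share is then 1 − 0.9⁹ = 61.3% and the ratio 0.613/0.190 = 3.2, little changed.

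The model is crude: it treats contacts as independent and every event as reportable at every contact. It shows the direction, and that the distortion is large when capture per contact is low and vanishes when capture is near complete.

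**4. After the fix.** If only answers to the same question at the 3- and 6-month visits are counted, k = 2 in both arms. The expected ratio is 1.00 for any c when true risks are equal.

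**The case against.** Several points on the other side are sound.

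- **No comparison is planned.** A reader might infer that events are to be compared between arms. Section 8.4 speaks only of recording them for each arm and states no contrast or test. This stands, although percentages set out by arm invite a comparison.
- **Bias is not established.** A reader might infer that the counts are biased. No section says that events will be taken from deliveries or the helpline. If they were recorded only at the shared visits, ascertainment could be equal. This stands. The text supports only that counts are open to unequal ascertainment if unsolicited reports are used, but nothing in the protocol restricts them to shared visits.
- **Absence is read from partial evidence.** Table 2 is a table of outcomes, and the Table 1 symbols are lost, so the rows and arm of the questionnaire item that allows time for questions cannot be fixed. This stands for that item. The legend is readable, though, and so are the empty control cells.
- **Arm-neutral information exists.** Table 2 makes no distinction by arm. Transaminases, creatinine, urea and hemogram are measured at baseline, 3 and 6 months, and AUDIT-C at baseline and 6 months. Reasons for withdrawal are recorded (7.4), one in four randomly selected subjects has a record review (8.2), and the health centre's doctors and nurses are collaborating researchers (5.2). It would therefore be too strong to say that nothing is ascertained equally. But none of these is designated as adverse-event capture, and the record review is written as data validation.
- **Section 5.7 gives two grounds.** The absence of interruption guidelines rests on the 6-month duration as well as on the expectation of no adverse effects, so it should not be attributed to the expectation alone.
- **Any ratio is assumed.** Taking a reporting probability of 0.6 to 0.8 for frequent contact and 0.3 to 0.4 for sparse contact would give 0.6/0.4 = 1.5 to 0.8/0.3 = 2.7, but that merely restates the inputs. The same caution applies to the table in the working.

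**Conclusion.** The concern holds in a limited form. Section 8.4 contemplates per-arm numbers, percentages and severity, but no scheduled item asks about events, and the eight extra rows, the 3-weekly deliveries and the helpline belong to the intervention arm alone. Followed as written, the per-arm percentages would rest largely on unsolicited reports with unequal opportunity by arm, probably tending towards more events under the intervention.

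The size cannot be derived from the documents. The illustrative ratios of 4.1 down to 1.01 depend on an assumed capture probability, on equal true risks and on counting each Table 1 row as a contact. The documents do not support the stronger conclusions that a biased between-arm comparison is planned or that a particular false excess will appear.

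The primary cholesterol analysis and the planned secondary analyses are unaffected. The change is a cheap improvement to data collection, not a correction to the trial's main inference.

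**What to change.** In section 5.8, add one row to Table 2: adverse events, asked with the same structured question of all participants in both arms, at 3 and 6 months.

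In section 8.4:
- replace 'contemplated' with 'recorded', so that collection is a commitment;
- state briefly what counts as an event and how severity is graded;
- base the per-arm number, percentage and severity on the 3- and 6-month answers only;
- list events volunteered through deliveries, other intervention-only contacts or the helpline separately, outside the per-arm percentages.

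The cost is one question at two visits that both arms already attend, plus a few lines of text. The downside is that more minor events will be reported overall.

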#### 8.5 STATISTICAL SOFTWARE

Analysis will be performed using R, Stata v.14 and Stata v.16.

